### Study population and recruitment

Women with endometriosis will be recruited from six hospitals in the Netherlands, including Radboud University Medical Centre, Amphia Hospital, Rijnstate Hospital, Jeroen Bosch Hospital, Catharina Hospital and St. Antonius Hospital. In all hospitals, a multidisciplinary centre for the diagnosis and treatment of endometriosis is present. Patients diagnosed with endometriosis will be invited to participate in the RCT by their gynaecologist. Those who are interested will be referred to a researcher to assess eligibility based on inclusion and exclusion criteria. HC women will be recruited at the Radboud University, Radboud University Medical Centre and via social media channels.

Eligible participants are women of at least 17 years old, with a confirmed diagnosis of endometriosis or adenomyosis through ultrasound, MRI or surgery, and experiencing pain symptoms with an NRS score >4 (this inclusion criterion is not attributable for HC women). Furthermore, they are nulligravida, premenopausal, have a body mass index (BMI) between 18 and 30 kg/m², scalp hair longer than 4 cm, commit to not change their use of dietary supplements, and willing to follow an AIDI and CBT. Additionally, eligible participants need to be proficient in Dutch.

Exclusion criteria are smoking, following a vegan diet, use of immunosuppressive or psychotropic medication or recurrent miscarriages (>2), a diagnosis of Crohn’s disease, ulcerative colitis, short bowel syndrome, another chronic inflammatory disease, coeliac disease, an eating disorder or a serious mental illness (DSM-V diagnosis).

Before inclusion, a food frequency questionnaire (FFQ), the ‘Eetscore’-FFQ, and a demographic questionnaire will be administered to potential participants. Those who meet the inclusion criteria will be offered informed consent (online supplemental material 1) by an authorised researcher. An independent researcher can be contacted if participants wish to discuss the study with an expert who is not directly involved in the research project but has knowledge about all aspects of the study. Participants can withdraw consent at any time.

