### Randomisation

After receiving signed informed consent, 1:1:1:1 computerised (Castor Electronic Data Capture (Castor EDC)) randomisation will take place to each of the four groups. An authorised researcher will be able to perform randomisation and have insight in the randomisation results. Stratification will be applied based on the following variables: hormonal use (yes/no), diagnosis of irritable bowel syndrome (yes/no), baseline Eetscore-FFQ outcome (<100/100 to 130), and baseline pain NRS average score (4 to 6/7 to 10). Randomisation within each stratum will be conducted to ensure comparability across groups for these factors.

This study is single blinded. Participants, nutritionist, and psychologists cannot be blinded due to the nature of the interventions, the assessor is blinded for the treatment allocation. Breaking the randomisation code will be done when patient’s health is at risk or when investigation is required by the sponsor, the Medical Ethics Committee (METC) Oost-Nederland or the monitor.

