### Statistical analysis

Data collected via questionnaires will be analysed using the software IBM SPSS V.29 for Microsoft Windows, data regarding the biological samples will be analysed using R software. The threshold for statistical significance is defined as <0.05.

For the primary outcome, pain NRS scores, repeated measures ANOVA will be conducted with time (T0 vs T2) as the within-participants variable, group (SC, SC + AIDI, SC + CBT, and SC + AIDI + CBT) as between-participant variable, and the pain NRS score as the dependent variable. If there are missing data, or a temporary study halt, a linear mixed model will be used instead of repeated measures ANOVA. Model fit will be assessed with residuals vs predicted plots and observed vs predicted plots. An intention-to-treat analysis will be followed in the case of follow-up losses. In this analysis, participants are analysed according to their original group assignment, regardless of whether they completed the treatment or dropped out, to minimise the risk of bias due to selective dropout. Given the random assignment of the intervention groups, a regression analysis on the pre-post change, adjusting for the pre-intervention score will be used to measure the main effect of the AIDI and CBT, and estimate interaction effects. Mediation analysis will be conducted to understand if and how secondary outcome measures mediate the effect of the intervention on the primary outcome.

To investigate the differences between women with and without endometriosis at baseline, a Welch’s ANOVA will be performed. This method is chosen to account for unequal group sizes and variances. In case the data are not normally distributed, a non-parametric Kruskal-Wallis test will be used.

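### Hormonal use, IBS and Eetscore stratify the randomisation but appear in no named model for pain; adding them is a nearly free gain, and the strata limits need reconciling with eligibility

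*Protocol article*

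**What the plan says.** The Randomisation section of the Protocol article describes allocation as "1:1:1:1 computerised (Castor Electronic Data Capture (Castor EDC)) randomisation will take place to each of the four groups". The strata are then listed: "Stratification will be applied based on the following variables: hormonal use (yes/no), diagnosis of irritable bowel syndrome (yes/no"), followed by "baseline Eetscore-FFQ outcome (<100/100 to 130), and baseline pain NRS average score (4 to 6/7 to 10"). These are four binary factors, hence 16 strata.

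The Statistical analysis section names three models for the pain score:
- a "repeated measures ANOVA will be conducted with time (T0 vs T2) as the within-participants variable" and group as the between-participant variable, with no covariate mentioned;
- a linear mixed model in its place if data are missing or the study is halted temporarily, again with no covariate mentioned;
- a regression of the change score, described as "adjusting for the pre-intervention score will be used to measure the main effect of the AIDI and CBT"; the same model is meant to give the interaction.

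Hormonal use, IBS and Eetscore appear in none of them. Baseline pain is covered only in the regression, through the pre-intervention score.

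On eligibility, the Study population and recruitment section requires "experiencing pain symptoms with an NRS score >4" without naming the NRS item. The Eetscore is obtained early ("Before inclusion, a food frequency questionnaire (FFQ), the ‘Eetscore’-FFQ, and a demographic questionnaire will be administered to potential participants"), but the listed criteria contain no Eetscore limit.

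**The concern.** Stratified allocation balances the chosen factors across arms. Where those factors predict the outcome, this lowers the true variance of the treatment estimate. A model that leaves them out keeps their variance in the residual, so it does not credit that reduction: the reported standard error exceeds the true one, intervals are too wide and the test rejects less often than its nominal level. Putting the factors in the model recovers the precision that the design has already created. At stake is some power, mainly for comparisons of single arms and for the interaction, which are the least precise contrasts in the plan.

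A second, smaller matter is that the strata and the stated criteria do not line up. This leaves unclear who fits which stratum.

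**Working it through.** **Inputs from the Sample size calculation section.** Effect 1.14, equal to 0.6 SD, so SD = 1.14/0.6 = 1.90. Pre-post correlation 0.3. 40 analysed per arm. Stated precision for the main effects 0.405 with power above 80%; stated interaction SE 0.57, interval ±1.12. The significance threshold is 0.05, taken as two-sided, which the ±1.12 supports.

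**Reproducing the plan's figures.**
- Residual SD with baseline adjustment: 1.90 × √(1 − 0.3²) = 1.812.
- SE, 40 against 40: 1.812 × √(2/40) = 0.405. Power: Φ(1.14/0.405 − 1.96) = 80.3%.
- Interaction SE: 1.812 × √(4/40) = 0.573; interval 1.96 × 0.573 = ±1.12.

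All the stated figures reproduce with adjustment for the baseline score alone. They therefore do not depend on the other stratification factors. The article attaches 0.405 to the main effects, but it is the SE for one arm against one arm. The pooled factorial contrast (80 against 80) has SE 1.812 × √(2/80) = 0.287 and power 97.8%.

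**Effect of adding the three factors.** Let R² be the share of that residual variance explained by hormonal use, IBS and Eetscore. The documents give no value, so 0 to 15% is an assumption. Each adjusted SE is the one above times √(1 − R²). With balanced strata, the large-sample type I error of the model that omits the factors is 2Φ(−1.96/√(1 − R²)).

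| Assumed R² | √(1 − R²) | SE 40 v 40 | Power 40 v 40 | Interaction SE | Power 80 v 80 | Type I error if omitted |
|---|---|---|---|---|---|---|
| 0 | 1.000 | 0.405 | 80.3% | 0.573 | 97.8% | 0.050 |
| 5% | 0.975 | 0.395 | 82.3% | 0.559 | 98.3% | 0.044 |
| 10% | 0.949 | 0.385 | 84.3% | 0.544 | 98.7% | 0.039 |
| 15% | 0.922 | 0.374 | 86.2% | 0.528 | 99.1% | 0.034 |

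The adjusted SE is thus 2.5–8% smaller for R² of 5–15%. Put the other way, the unadjusted SE is 1/√(1 − R²) − 1 = 2.6–8.5% larger than it need be.

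**Simulation check.** 4,000 trials per scenario, N = 160, 16 strata, permuted blocks of 4 (an assumption, as the article names no block scheme). Type I error without adjustment was 0.048, 0.045 and 0.039 at R² of 0, 5% and 10%; with adjustment it was 0.048, 0.051 and 0.046. At R² = 10% the unadjusted model reported a mean SE of 0.406, while the estimates varied with an SD of 0.384–0.390. At R² = 0 the mean SE was 0.4050 without the three terms and 0.4054 with them. The residual degrees of freedom fall from 160 − 5 = 155 to 152.

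**Strata against eligibility.**
- Pain: the criterion is a score above 4 on an unnamed item; the lower stratum is an average score of 4 to 6. The Variables section measures most intense, average and symptom-specific pain. If the criterion means average pain, a score of 4 has a stratum but is not eligible. If it means another item, such as most intense pain, an eligible woman could also have an average below 4 and no stratum.
- Eetscore: the strata are below 100 and 100 to 130. A score above 130 has no stratum and is not excluded by any stated criterion.

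**The case against.** The strongest objection is that this is a condensed article: a full protocol (version 7) exists and an analysis plan may exist, and covariate lists are often settled there. The article does not say that no other term will enter. This stands as a limit on the point. However, the article does name the adjustment for its regression, and names the baseline score alone.

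Second, the harm is conditional. The Randomisation section gives comparability across groups as the reason for stratifying; it does not say that the factors predict pain. With R² = 0, omission changes nothing. This stands.

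Third, the regression is not clearly the primary model, since the repeated measures ANOVA is named first. This also stands, but the three factors are absent from every model named.

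Some stronger readings are tempting:
- A reader might infer that the test is invalid or the trial underpowered. The documents do not support this: any error is in the conservative direction, and the stated precision and power reproduce without these factors.
- A reader might infer that four factors are ignored. Average pain is covered by the continuous baseline score wherever that score is adjusted for and average pain is the outcome.
- A reader might attach the gain from 80% to 82–86% to the factorial main effect. It belongs to one arm against one arm; the pooled effect has little left to gain.
- A reader might infer that the Eetscore strata contradict an eligibility rule, or that eligible women cannot be randomised. No Eetscore rule is stated, and the full protocol may hold a cap.

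**Conclusion.** The point holds as a nearly costless improvement, not as an error that threatens the conclusions. Three stratification factors are in no named model. If they are prognostic and allocation is balanced within strata, leaving them out makes the reported SE a few per cent too large, with no bias and no inflated type I error.

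With an assumed R² of 5–15%, power for a single-arm comparison would rise by about 2 to 6 percentage points, and the interaction SE would fall from 0.573 to between 0.559 and 0.528. These sizes depend on the assumed R², on the plan's SD of 1.90 and correlation of 0.3, and on 40 analysed per arm. They describe the baseline-adjusted regression, the analysis that the planning figures match.

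The strata matter is a request for reconciliation: the pain item is unnamed in the criterion, and the upper Eetscore limit has no counterpart in the stated criteria.

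**What to change.** In the model used for the AIDI, CBT and interaction effects, add hormonal use, IBS and baseline Eetscore (continuous or by stratum) next to the continuous T0 average NRS. If a repeated-measures or mixed model is kept, enter the factors with their interaction with time, because the treatment contrast there is a difference in change.

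Reconcile the Study population and recruitment section with the Randomisation section: name the NRS item in the pain criterion and make its limit agree with the stratum. For the Eetscore, either state the limit that the stratum of 100 to 130 implies or label that stratum so that it covers all eligible scores. Which limits apply is for the investigators to decide.

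The cost is a sentence in the analysis text and one line in the strata or criteria. No new data are needed, because all four factors must be known at randomisation. The model gives up 3 of about 155 degrees of freedom. The change should be fixed before outcome data are examined by arm.

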**Methods and analysis:**

The Pain in Endometriosis And the Relation to Lifestyle (PEARL) study is a five-arm randomised controlled trial with a pre-post factorial design with two factors: an AIDI and CBT. The study population will consist of 250 premenopausal women, of whom 200 are diagnosed with endometriosis and experience pain symptoms and 50 are healthy controls (HC). Women with endometriosis will be recruited from one academic tertiary and five secondary hospitals in the Netherlands. They will be randomised (1:1:1:1) among four intervention groups: standard care (SC) (SC group), SC and an AIDI (SC + AIDI group), SC and CBT (SC + CBT group), and SC, AIDI and CBT (SC + AIDI + CBT group). Women with endometriosis will visit the hospital twice during the intervention period, at the start (T0) and end (T2) of the 13-week intervention period. HC will not undergo any of the interventions and will have one hospital visit (T0). Participants will complete questionnaires regarding pain symptoms, HRQoL, physical activity level, sleep, diet quality, pain cognitions, and stress at T0 and T2. Furthermore, they are instructed to collect menstrual effluent, a vaginal swab and a faecal sample. During the study visits, peripheral blood will be drawn and scalp hair samples will be taken. The primary outcome is average pain, measured using a numerical rating scale. Secondary outcomes focus on HRQoL, inflammation, immune system characteristics, vaginal- and gut microbiome, and hair cortisol levels. These are considered to reflect potentially underlying mechanisms of the effect of both interventions on the primary outcome. Biological samples and questionnaires of women with endometriosis and HC will be compared to establish the differences in secondary outcomes.

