### Variables

The primary outcome of this study is the pain intensity score, measured with NRS, to assess the most intense pain and the average pain during last month, and endometriosis-specific pain symptoms (eg, dyspareunia, dyschezia, gastrointestinal symptoms) on a 0–10 point scale.

Secondary outcome variables are considered to reflect potentially underlying mechanisms of the effect of both interventions on the primary outcome. We will investigate the influence of the AIDI, CBT, and the combination of both interventions on inflammatory markers and immune cell composition in PB and ME, the vaginal and gut microbiome, and hair cortisol levels. Furthermore, HRQoL will be assessed with the Endometriosis Health Profile-30 (EHP-30) and Short Form Healthy Survey-36 (SF-36).

Demographic variables will be recorded including age, height, weight, waist circumference, BMI, marital status, education level, occupation, the method used to diagnose endometriosis, year of diagnosis, type of endometriosis, use of contraception, use of analgesics, use of medication, presence of subfertility, parity, diet history, history of eating disorders, history of (self-reported) intestinal disorders, history of DSM-V diagnosis, and if patients underwent psychological treatment prior to inclusion in this study.

Additional outcome variables are pain anxiety which will be measured with the Pain Anxiety Symptom Scale (PASS), and pain catastrophising which will be measured by the Pain Catastrophising Scale (PCS). Moreover, sleep and physical activity level are assessed to minimise confounding factors. Therefore, participants will fill in the Pittsburgh Sleep Quality Index to assess sleep quality and the International Physical Activity Questionnaire Short Form to assess physical activity level. Additionally, fatigue is measured using the Checklist Individual Strength. Self-reported stress levels will be measured with the Perceived Stress Scale. The central sensitisation of pain is assessed using the Central Sensitisation Inventory. To assess the consistency of participants in adhering to their diet and to determine whether participation in the study prompts premature dietary changes, the Eetscore-FFQ will be administered three times throughout the intervention period. Patients’ experience following the AIDI and/or CBT will be measured with an evaluation questionnaire.

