All primary, secondary, and additional variables will be measured at baseline (T0) and after the intervention period of 13 weeks (T2). Women with endometriosis will visit the hospital twice during the intervention period, at the start (T0) and end (T2) of the study. HC will not undergo any of the interventions and will have one hospital visit (T0). During the study visits PB will be drawn, scalp hair samples will be collected, and participants will hand in ME, a vaginal swab, and faecal sample.

Halfway through the study period (T1), for an interim measurement, women with endometriosis will fill in the Eetscore-FFQ, as part of an adherence measurement. In addition, they will be asked to complete the pain NRS and EHP-30.

To evaluate the long-term feasibility, cost-effectiveness and impact of the interventions, women with endometriosis will be asked to complete the pain NRS, EHP-30, and Eetscore-FFQ at 6 months after completing the study (T3).

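### The mediation plan takes its mediators from the secondary outcomes, which brings in quality of life and leaves out the self-reported targets of CBT

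*Protocol article*

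**What the plan says.** The Statistical analysis section gives mediation one sentence: "Mediation analysis will be conducted to understand if and how secondary outcome measures mediate the effect of the intervention on the primary outcome". The mediators are thus defined by class, as the secondary outcomes.

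Membership of that class is stated twice. The abstract says "Secondary outcomes focus on HRQoL, inflammation, immune system characteristics, vaginal- and gut microbiome, and hair cortisol levels" and continues "These are considered to reflect potentially underlying mechanisms of the effect of both interventions on the primary outcome", so quality of life is on the list that is called mechanistic. The Variables section repeats that "Secondary outcome variables are considered to reflect potentially underlying mechanisms of the effect of both interventions on the primary outcome", lists the biological markers, and ends the same paragraph with the quality-of-life instruments: "HRQoL will be assessed with the Endometriosis Health Profile-30 (EHP-30) and Short Form Healthy Survey-36 (SF-36").

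A later paragraph of that section opens a different class: "Additional outcome variables are pain anxiety which will be measured with the Pain Anxiety Symptom Scale (PASS), and pain catastrophising". The Perceived Stress Scale is in the same paragraph.

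On timing, the Variables section says "All primary, secondary, and additional variables will be measured at baseline (T0) and after the intervention period of 13 weeks (T2"). At T1 the women complete the Eetscore-FFQ, the pain NRS and the EHP-30. No T1 measurement of SF-36, PASS, PCS, perceived stress or any biological marker is listed.

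**The concern.** A mediator has to lie on the causal path from intervention to outcome. Quality of life is a doubtful candidate for the path to pain, because worse pain is an obvious cause of worse quality of life. If the arrow runs from pain to quality of life, the two correlate within arm and the intervention moves both. A standard regression mediation analysis then reports an indirect effect through quality of life that is not there.

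The same classification works the other way for CBT. Its measured psychological targets are not in the class from which mediators are drawn. An analyst who follows the text would test quality of life as a mediator of the CBT effect and would not test catastrophising or pain anxiety. At stake are the mechanistic conclusions. The Strengths and limitations box promises insight into psychological as well as biological mechanisms, and the analysis as written gives little of the former.

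**Working it through.** **1. Class of each variable against the article's own causal account**

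| Measure | Class in Variables | In the stated mediator set? | Role the article gives it |
|---|---|---|---|
| Inflammatory, immune and microbiome markers | secondary | yes | biological mechanism (end of Introduction) |
| Hair cortisol | secondary | yes | same list; an indirect marker of stress |
| EHP-30, SF-36 | secondary | yes | a result of lower inflammation beside pain relief (Abstract, Introduction); affected by the burden of the disease and by pain cognitions (main Introduction) |
| PASS, PCS | additional | no | measure what CBT is said to reduce (main Introduction) and are used to personalise it (Cognitive behavioural therapy section) |
| Perceived Stress Scale | additional | no | stress is part of the CBT sessions (same section) |

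The passages cited for quality of life do not present it as a cause of pain.

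**2. Timing**

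The NRS asks about the last month. At T2 the pain score therefore covers a period that has largely passed when the T2 mediator is recorded. EHP-30 also has a T1 value, but it is taken alongside the T1 NRS, and the mediation sentence assigns T1 no role. SF-36 has no T1 value.

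**3. Size of the artefact in the worst case**

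The article gives no figure for mediation. The scale comes from its Sample size calculation section:

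- Effect 1.14 = 0.6 SD, so SD = 1.14 / 0.6 = 1.9.
- Pre-post correlation 0.3, so the baseline-adjusted residual SD is s = 1.9 × √(1 − 0.3²) = 1.812.
- Check: 1.812 × √(2/40) = 0.405, the article's stated precision. The scale is the authors' own.

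Suppose quality of life M is caused only by T2 pain Y, so that true mediation is zero. Let ρ be their within-arm correlation after adjustment for baseline pain. Write M = Y + noise, with noise variance s²(1/ρ² − 1). The residual SD of M is then s/ρ.

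- Intervention on M: a = c, the total effect on pain.
- M on Y given the intervention: b = ρ × s / (s/ρ) = ρ².
- Apparent indirect effect: a × b = cρ². Apparent share mediated: ρ².

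The article does not give ρ, so a range is assumed. The simulation compared 80 with 80 (one factor of the 2×2 at 40 per arm), with effect −1.14, adjustment for T0 pain and 2,000 runs:

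| ρ (assumed) | ρ² | ρ² × 1.14 (NRS points) | Simulated share | Both paths significant |
|---|---|---|---|---|
| 0.3 | 9% | 0.10 | 8.9% | 22% |
| 0.5 | 25% | 0.29 | 25.4% | 53% |
| 0.7 | 49% | 0.56 | 49.0% | 79% |

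A separate simulation with 160 women, no baseline term and a Sobel test (3,000 runs) gave the same shares. It rejected in 12%, 44% and 74% of runs at ρ = 0.3, 0.5 and 0.7. The rejection rate depends on the test; the false share does not. As the table shows, adjusting for T0 pain does not remove the artefact.

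**The case against.** The strongest reply is that this is one sentence in a condensed article. Models, time points and covariates can be left to the full protocol or an analysis plan. That holds for those details, and their absence is not criticised here. The class of mediators is stated, however, and a plan that follows the text would inherit it.

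A second reply is that the intent was narrower. The end of the Introduction describes a biological mechanism and lists only biological markers, and the Variables section adds quality of life after them as a further item. Loose wording may well be the cause. Even so, the abstract calls the whole list mechanistic, quality of life included, and the analysis sentence makes no exception.

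Some stronger readings are tempting, and the document does not support them:

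- *Quality of life is solely a consequence of pain.* The Introduction says that the disease and pain cognitions affect it. It does not say that pain is its only cause, so the ρ² figures are an upper case and not an expected bias.
- *Quality of life is measured only at the same visit as the outcome.* EHP-30 is also collected at T1, so a lagged model with T2 pain is possible, though not planned in the text. It would not by itself settle direction, because pain is measured at T1 too.
- *No CBT pathway is left in the analysis.* Hair cortisol is a secondary outcome and keeps an indirect stress pathway in. What is missing is the self-reported targets.
- *Exchanging quality of life for PCS, PASS and perceived stress solves the problem.* These are listed only at T0 and T2, and the Introduction calls the relation between stress and endometriosis bidirectional. Reverse causation threatens them as well.

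**Conclusion.** The point stands as a misclassification in the stated mediation analysis. As written, it admits quality of life as a mediator of pain, against the article's own causal account, and leaves out the self-reported measures of what CBT is meant to change.

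The artefact for quality of life is at most about ρ² of the effect, or 9% to 49% for assumed correlations of 0.3 to 0.7. That bound assumes pure reverse causation, linear models, and mediator and outcome both taken at T2. If quality of life depends only partly on pain, the artefact is smaller. The omission for CBT needs no assumption, since it follows from the variable classes.

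The primary comparison, the sample size and the data collection are unaffected. Only the mechanistic conclusions are at risk.

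**What to change.** Change the wording in the abstract, the Variables section and the Statistical analysis section:

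- State that EHP-30 and SF-36 are outcomes and not mediators.
- Name the candidate mediators by intervention: inflammatory, immune and microbiome markers for the AIDI; PCS, PASS and perceived stress, with hair cortisol, for CBT.
- Adjust for the T0 value of the mediator and the T0 NRS. The exact models can be set out in the analysis plan.
- Report mediation from mediators and pain both measured at T2 as exploratory association, for the CBT measures as much as for the biological ones, because temporal order is not established for either.

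All the variables are already collected, so no visit or questionnaire is added. The downside is fewer and weaker mediation claims. The change should be made before outcome data are examined, because adding PCS and PASS as mediators afterwards would look post hoc.

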Thus, supporting women with endometriosis through lifestyle interventions may be crucial for symptom management and improving HRQoL. Therefore, the Pain in Endometriosis And the Relation to Lifestyle (PEARL) study examines the effects of two lifestyle interventions: an AIDI and CBT, on endometriosis-related symptoms and HRQoL. Both interventions are tested separately, as well as in conjunction with one another, to examine whether the combination of these interventions has an enhancing effect. To explore a possible underlying biological mechanism as a contributing factor for symptom improvement, the gut and vaginal microbiome, hair cortisol levels, inflammatory markers and immune cell composition in peripheral blood (PB), and menstrual effluent (ME) are being analysed before and after the interventions. In addition, this study aims to identify differences in these biomarkers between women with and without endometriosis to gain a deeper understanding of the pathogenesis of endometriosis. We assume that this will contribute to new insights in diagnostics and potential new treatment strategies for women with endometriosis.

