### Interventions

#### Standard care

The two primary components of standard care for endometriosis include the use of analgesics, like paracetamol or non-steroidal anti-inflammatory drugs or morphine. Moreover, another component is the use of hormonal therapies, such as oral contraceptives, progestogens or gonadotrophin‑releasing hormone analogues or antagonists. Standard care is individualised based on the participants’ needs and physicians’ choice.

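### The exploratory comparison with healthy controls is tied to tests that cannot adjust, so a marker difference can reflect hormone use if use differs between the groups

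*Protocol article*

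**What the plan says.** All references are to the protocol article.

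- **Aim (Introduction).** The text says that "this study aims to identify differences in these biomarkers between women with and without endometriosis" and expects this to inform understanding of how the disease arises, its diagnosis and possible new treatments.
- **Status (Sample size calculation).** The comparison is labelled exploratory. The control group of 50 rests on a published rule of thumb of 30 to 50, not on a power calculation.
- **Source of the groups (Study population and recruitment).** Patients come from six hospitals, each with an endometriosis centre. For controls, "HC women will be recruited at the Radboud University, Radboud University Medical Centre and via social media channels". Hormone use is not an exclusion for either group.
- **Hormone use in patients (Standard care).** Analgesics are one of two main components, and "another component is the use of hormonal therapies, such as oral contraceptives, progestogens" and similar agents. Under Randomisation, hormone use is a stratification factor, which concerns only the four randomised arms.
- **Analysis (Statistical analysis).** The sentence that begins "To investigate the differences between women with and without endometriosis at baseline" names Welch's ANOVA. The reason given is: "This method is chosen to account for unequal group sizes and variances". If normality fails, "a non-parametric Kruskal-Wallis test will be used". The general rule is: "The threshold for statistical significance is defined as <0.05".
- **Data available (Variables).** Age, BMI, contraception and medication are recorded.

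**The concern.** This is the one comparison in the trial that randomisation does not protect, and it is the one given tests with no place for covariates. The randomised comparison, by contrast, includes a regression adjusted for the baseline score. Welch's method deals with unequal variances and group sizes, which is the reason the article gives for it. It does nothing about a systematic difference between the groups in something other than disease.

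Hormone use is the candidate that the article itself supports. It is part of how patients are treated, it was thought important enough to stratify on, and the Introduction links oestradiol to the inflammatory environment. If patients and controls differ in hormone use, the unadjusted contrast mixes a treatment effect with a disease effect. The result could then be read as evidence on pathogenesis or as a diagnostic lead.

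This is not a detail left to a later analysis plan. The article names the method, and the named method cannot adjust.

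**Working it through.** **No planned figure to reproduce.** The article gives no precision or power figure for this comparison, only the group sizes.

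**Inputs from the article:** 200 women with endometriosis, 50 controls, threshold 0.05 (taken as two-sided, since the side is not stated).

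**Assumed inputs, not in the article:** the effect of hormone use on a marker, h, in SD units (0.3 to 0.8), and the share of hormone users among patients, pE, and controls, pH.

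**Step 1, precision.** SE = √(1/200 + 1/50) = √0.025 = 0.158 SD. The difference detectable with 80% power is (1.96 + 0.842) × 0.158 = 0.44 SD.

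**Step 2, bias.** With no disease effect at all, the unadjusted difference has expectation b = (pE − pH) × h. For h = 0.5 and a 40-point difference, b = 0.40 × 0.5 = 0.20 SD. If pE = pH, then b = 0.

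**Step 3, chance of a significant result without a disease effect.** P = Φ(b/SE − 1.96) + Φ(−b/SE − 1.96). For b = 0.20, b/SE = 1.265, so P = Φ(−0.695) + Φ(−3.225) = 0.244. The ends of the assumed range are b = 0.20 × 0.3 = 0.06 (P = 0.067) and b = 0.60 × 0.8 = 0.48 (P = 0.859).

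**Step 4, check by simulation.** 4,000 runs per scenario, no disease effect, three values of h (0.3, 0.5, 0.8):

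| Hormone use, patients vs controls | Bias (SD) | Welch, false positives | Model adjusted for hormone use |
|---|---|---|---|
| 50% vs 50% | 0 | 4–5% | about 5% |
| 60% vs 40% | 0.06–0.16 | 6–14% | about 5% |
| 70% vs 30% | 0.12–0.32 | 11–47% | 5–6% |
| 80% vs 20% | 0.18–0.48 | 20–82% | about 5% |

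Kruskal-Wallis gave nearly the same rates as Welch. At 70% vs 30% with h = 0.5, the Welch rate was 23.5%, against 24.4% from the formula. The formula runs slightly high at the top because hormone use also adds variance to the marker. At 80% vs 20% with h = 0.8, that added variance is 0.8² × 0.8 × 0.2 = 0.102, so SE = √(0.025 × 1.102) = 0.166 and P is about 0.82, as simulated.

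**Step 5, price of adjusting.** The SE of the group term grows by 1/√(1 − R²), where R² is the squared correlation of group with hormone use.

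- 70% vs 30%: overall use is (140 + 15)/250 = 0.62; R² = (0.16 × 0.4)² / (0.16 × 0.62 × 0.38) = 0.109; the SE rises from 0.158 to 0.167.
- 80% vs 20%: overall use is (160 + 10)/250 = 0.68; R² = (0.16 × 0.6)² / (0.16 × 0.68 × 0.32) = 0.265; the SE rises to 0.184.

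**The case against.** **The comparison is exploratory.** This stands and lowers the weight of the point. It excuses limited power. It does not excuse a bias that data already collected could expose, because bias does not shrink with sample size and the Introduction attaches substantive aims to the comparison.

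**Controls may use hormones too.** This also stands. Oral contraceptives are among the listed therapies and premenopausal controls may take them. Stratifying on hormone use shows that it varies among patients, not that it differs from controls. A reader might infer that the comparison is confounded. The article supports only that it can be.

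**Eligibility already narrows other differences.** The explicit exemption for controls is attached to the pain criterion. Read as written, the requirements to be premenopausal, nulligravida, BMI 18 to 30, non-smoking and not vegan apply to controls as well. A reader might infer that age and diet confound the contrast just as seriously. The article gives no such support.

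**Silence on matching is not a statement that there is none.** Correct. The article condenses a longer protocol. What can be said is that no matching or adjusted model is described and that the named tests cannot adjust.

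**Adjustment can remove part of the disease difference.** This is the most important objection. Hormones are prescribed because of the disease, and the Introduction reports that many women change diet in response to it. Conditioning on either changes the question. This argues for showing estimates side by side, not for leaving the unadjusted test alone.

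**The switch to Kruskal-Wallis.** A reader might see a separate fault here. With error rates nearly the same as Welch's, it adds nothing material.

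**Conclusion.** The point holds in a limited form. The analysis named for the patient-control comparison cannot separate disease from hormone use, and the article gives grounds to think that hormone use could differ. Whether it does, and by how much, is unknown.

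The 0.20 SD bias and the 24% false-positive rate illustrate one pair of assumptions (0.5 SD effect, 40-point difference in use). The wider span of 7 to 86% by formula, or up to 82% by simulation, shows only how strongly the answer depends on those assumptions. It is not an estimate of this trial's error rate, and the rate is the nominal 5% if use is equal.

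A reader might infer that the trial's main result is weakened. It is not: the four randomised arms are compared with each other and do not depend on the controls. The change is worth making because it is cheap and the data are recorded, within the limits of an exploratory analysis.

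**What to change.** Replace the Welch or Kruskal-Wallis rule for this comparison with the following, set down before the baseline data are analysed:

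1. For each suitable continuous marker, transformed if needed, fit a linear model with heteroscedasticity-robust standard errors: group, adjusted for age and BMI. Robust errors keep the protection against unequal variances that motivated Welch.
2. Beside it, report the same model with hormone use (yes/no) added.
3. Add an analysis stratified by hormone use or restricted to non-users.
4. Treat adjustment for the baseline Eetscore as a sensitivity analysis only, because diet may change in response to the disease.
5. Tabulate hormone use by group and report results as associations. Draw conclusions on pathogenesis or diagnosis only where a difference persists after hormone use is accounted for.

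Markers that do not suit a linear model, such as microbiome composition, need their own method, with the same pair of estimates.

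**Cost.** Wording and a few degrees of freedom; no new data. Intervals widen, modestly in the two cases worked above and more if hormone use is nearly confined to patients. That would itself show that the data cannot separate disease from treatment. The hormone-adjusted estimate may over-adjust, since hormone use can follow from the disease, which is why both estimates should be shown.
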